## 2. Materials and Methods

### 2.1. Study Design, Setting, and Sample Size

This is a single-center open-label two-arm randomized controlled crossover superiority trial (RCCT) adhering to CONSORT guidelines [39] with a total duration of 20 weeks (Supplementary Material). The study is conducted at the Swiss Paraplegic Research in Nottwil, Switzerland. It involves two 8-week interventions consisting of daily intake of either a probiotic (Biotics-G, Burgerstein AG, Rapperswil-Jona, Switzerland) or a prebiotic (Oat Bran, Naturaplan, manufactured by Swissmill, Zurich, Switzerland) supplement, separated by a 4-week washout period (Figure 1). Group allocation, which determines the order of supplement intake by the participants, is determined using a permuted block randomization (block size 4). For this, a randomization list was created using the statistical software Stata (Stata. Version 18. College Station, TX, USA: StataCorp, 2024). Due to the nature of the supplements, no allocation concealment or blinding of study personnel or participants is possible. Recruitment for this study started in summer 2025, and data collection will continue for two years; the study is therefore expected to end in summer 2027. The low-risk nature of this study warrants a risk-based approach for study monitoring. The study will be conducted in accordance with the Declaration of Helsinki. The study was approved by the Ethics Committee for Northwest/Central Switzerland (EKNZ, ID: 2025-00238, 24 February 2025, Version 2.0). The study is registered at ClinicalTrials.gov (ID: NCT06870331, 2 April 2025). Written informed consent will be obtained from all participants involved in the study.

The sample size was calculated for the primary outcome (changes in GIQLI) based on the results of a previous pilot study [34], applying a clinically relevant mean difference of 10 points on the GIQLI [40,41,42] and correcting for a larger expected variability in the GIQLI in the current study population. Assuming a significance level of 5% and a power of 85%, a sample size of 50 participants, with 25 participants in each group, was determined.

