### 2.2. Study Participants

Adult (≥18 years old) male and female individuals with chronic (>1 year) traumatic and non-traumatic SCI, with a complete or incomplete lesion according to the American Spinal Injury Association Impairment Scale (AIS A-D), are invited to participate. Individuals experiencing significant GI complaints, indicated with ‘yes’ at screening and a GIQLI score below 110 at baseline (T1), are included. Exclusion criteria are antibiotic use, major dietary changes within 4 weeks before the study, presence of a diagnosed clinically relevant medical condition (e.g., Crohn’s disease, diagnosed eating or GI disorders), intake of significant concomitant medication (e.g., immunomodulating therapy, mesalazines), and pregnancy. No concurrent participation in other clinical trials investigating or potentially affecting GI health is allowed. Non-adherence to the supplementation, defined by missing >25% of supplement doses, can lead to exclusion from the trial at the investigator’s discretion.

Potential participants are recruited by distributing the study information and a flyer within the networks of the Swiss Paraplegic Association, the Swiss Paraplegic Centre, and the Swiss Paraplegic Research. In the case of a low recruitment rate, study information will also be spread through community platforms, both online and in magazines (e.g., Paracontact). Interested participants are contacted by phone or in person to perform the screening, where eligibility criteria are assessed, and the participant is informed about the study and what procedures it entails. Written participant information and an informed consent form are provided. After at least 24 h of consideration time, informed consent will be obtained from each participant.

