### 2.3. Intervention

The probiotic intervention involves an 8-week supplementation with the commercially available probiotic BIOTICS-G (Burgerstein AG, Rapperswil-Jona, Switzerland). Participants take one sachet (2.5 g) daily, mixed into 50–100 mL of water 30 min before breakfast or dinner. Biotics-G supplies fourteen lactobacilli and bifidobacteria strains together with Saccharomyces boulardii, delivering 2.5 × 10^9^ CFU per sachet. The composition closely mirrors Bactosan^®^ Pro-FOS, which improved microbial diversity and reduced systemic inflammation in a crossover pilot study involving wheelchair athletes with spinal cord lesions [35]. Bactosan^®^ Pro-FOS is no longer on the Swiss market, which is why the alternative probiotic BIOTICS-G had to be chosen. The present trial extends that evidence to a community cohort.

The prebiotic intervention involves taking a prebiotic supplement for 8 weeks. The participants take 5 g of oat bran daily (Oat Bran, Naturaplan, manufactured by Swissmill, Zurich, Switzerland), mixed in with their usual breakfast or dinner.

The probiotic supplementation serves as the intervention of interest and the prebiotic supplementation as an active comparator, based on the literature and a pilot study [35,43].

Participants are instructed to maintain their usual training routine and diet, to minimize the chance of potential health modifications to be attributable to any factor other than the intervention with pre- or probiotics. Participants receive weekly reminders to take supplements and are asked to return empty packages to the study center after the intervention periods as a means of control of adherence to supplementation.

The first intervention phase is followed by a 4-week washout period to prevent carryover effects. Previous studies in non-disabled individuals have proven 1–2 weeks to be sufficient for effects of inulin-type fructans (prebiotics) to disappear after the intake has ceased [44]. To ensure adequate washout in our study population, the washout period is extended to four weeks.

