## 3. Data Analyses

An intention-to-treat analysis will be conducted to minimize potential bias resulting from disruption to baseline equivalence following randomization, which may occur due to participant withdrawal, non-adherence to the study protocol, or excessive missing data. Participants will be included in analyses only where data are available. Protocol deviations, early withdrawals, and loss to follow-up will be documented and evaluated. Basic univariable statistical analysis techniques will be used to describe the study population as well as the primary and secondary outcomes at the different measurement points. To evaluate the longitudinal variation in the primary outcome and secondary outcomes, we will use multilevel mixed-effects models that appropriately account for the within- and between-individual sources of variance in outcome variation. In these models, participants are treated as random effects, while intervention and period are used as fixed effects. All models will be adjusted for the baseline value of the respective outcome measured before each period. To evaluate potential carryover effects, sequence (AB vs. BA) will be included as a fixed effect, and treatment-by-period interactions will be tested. Furthermore, pre-period baselines will be compared to verify that the gut environment returned to its SCI-baseline during washout, and a carryover term will be incorporated into the model to identify residual effects. If significant carryover is detected, a sensitivity analysis using only period 1 data will be performed to provide an unbiased estimate of the intervention effect. Depending on the findings, subgroup analyses may be performed for personal parameters (e.g., sex, lesion level). For the microbiome analyses, diversity indices will be compared using paired *t*-tests while correcting for multiple testing using the Benjamini–Hochberg method. A significance level of 5% will be applied. Protein concentrations will be reported as absolute abundances in pg/mL. Absolute abundance will be tested with mixed-effects models analogous to the primary analysis. The Benjamini–Hochberg procedure will control the false-discovery rate at 5%. Multi-omics integration will employ sparse partial least-squares regression to relate inflammatory proteins, microbial genera, and clinical outcomes (GIQLI, GITT). Statistical software packages to be used include R (Version 4.5.2), Stata (Version 19.0), and SPSS (Version 31.0), or any newer stable version available at the time of data analysis.

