The study is subject to several limitations. The open-label nature of the study might introduce a potential bias. With the probiotic packaging resembling a medicinal product, versus the prebiotic clearly coming from a grocery store, participants may have different expectations for the efficacy of either supplement, which may bias their responses. This is not preventable, given the need for specific packaging for both supplements. Additionally, as diet and lifestyle are not strictly controlled, microbiome changes may be confounded, which in a real-life setting cannot be avoided. Despite not being controlled, by assessing physical activity and nutrition at each timepoint, big lifestyle changes can be detected and taken into consideration when analyzing the data. Further, at home supplementation makes strict control of adherence impossible; however, by asking participants to return empty packages after the intervention period, a sense of control is added and quantification of adherence is possible.

Another potential limitation of this crossover design is the risk of carryover effects, where the physiological and microbial changes from the first intervention might persist into the second period. Given the neurogenic bowel dysfunction inherent in SCI, transit times are prolonged, which could theoretically extend the influence of interventions. However, this risk is mitigated by the implementation of a 4-week washout period, exceeding the 2-week window typically required for the microbiome to revert to baseline after a dietary perturbation, and by employing a rigorous four-tiered statistical framework to detect sequence and period interactions [57,58,59,60].

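### The period-1 analysis is run only after a significant carryover test, yet it is called unbiased; that property holds only if it is reported in every case

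*Protocol article*

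**What the plan says.** Section 3 (Data Analyses) fits mixed models with participant as random effect, intervention and period as fixed effects, and adjustment for the outcome value before each period. For carryover, "sequence (AB vs. BA) will be included as a fixed effect, and treatment-by-period interactions will be tested". It adds that "pre-period baselines will be compared to verify that the gut environment returned to its SCI-baseline during washout", and it also puts a carryover term in the model, with no condition attached. Then comes the rule at issue: "If significant carryover is detected, a sensitivity analysis using only period 1 data will be performed to provide an unbiased estimate".

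Section 4 (Strengths and Limitations) says the carryover risk is mitigated partly "by employing a rigorous four-tiered statistical framework to detect sequence and period interactions". Section 2.1 gives the only sizing figures: a 10-point GIQLI difference and "Assuming a significance level of 5% and a power of 85%, a sample size of 50 participants, with 25 participants in each group". No SD or within-person correlation is given.

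**The concern.** Three statements promise more than the design can deliver.

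1. Period 1 alone is free of carryover and, if always reported, unbiased. Reporting it only when a correlated test is significant selects among trials. The selected estimates need not centre on the truth, and their 95% intervals need not cover at 95%.
2. The sequence, treatment-by-period and carryover terms are presented as separate layers of protection, but in a two-sequence, two-period design they are a single contrast.
3. A non-significant T3 comparison is said to verify a return to baseline, which absence of significance cannot do at 25 per sequence.

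At stake is how a reader weighs the carryover check. A selected figure would be printed as unbiased, and a non-significant result would be read as proof of washout.

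**Working it through.** **Number of distinct checks.** Four sequence-by-period cells support four fixed effects. Intercept, period and treatment use three. Write AB1 for the mean of sequence AB in period 1, and so on.
- A carryover term (residue of A in AB2) has coefficient AB2 − BA2 + AB1 − BA1.
- The sequence effect is that same sum up to scale, and so is the treatment-by-period interaction.
- With the T3 comparison there are therefore two distinct checks if T3 is compared between sequences. A comparison of T3 with each participant's own T1 would be a further variant of the baseline check.

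**Inputs.** From section 2.1: 10 points, 5% (taken as two-sided), 85% power, 25 per sequence. Back-solving with the t distribution:
- 50 paired differences with SD 23.1 give power 0.851;
- 25 vs 25 with SD 11.6 gives power 0.848.

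Both reproduce the stated 85%. Assumed: within-person correlation r of 0.5 or 0.7, and equal SD s at every visit. The SD of a within-person difference is s√(2(1−r)). SD of difference 23.1 with r = 0.7 would need s = 29.8, hard to reach with entry limited to scores below 110, so it is left out.

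**T3 comparison between sequences, adjusted for T1.**
- SE = s·√(1−r²)·√(2/25). The T1-adjusted period-1 estimate has the same SE.
- Their correlation is r/(1+r): 0.33 at r = 0.5, 0.41 at r = 0.7.
- For residue L at T3, put a = 2.01 − L/SE and b = 2.01 + L/SE. Let P be the sum of the normal tail areas above a and b. The expected shift of the period-1 estimate, given significance, is [r/(1+r)]·SE·[φ(a) − φ(b)]/P.
- Setting A, L = 5: SE = 23.1 × 0.866 × 0.283 = 5.66; L/SE = 0.88; a = 1.13; shift = 0.333 × 5.66 × 1.56 = 2.9.

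| Setting | s | r | SD of difference | SE | Power for 5 points | Period-1 mean after significant T3 (residue +5 / −5; truth 10) | 95% half-width |
|---|---|---|---|---|---|---|---|
| A | 23.1 | 0.5 | 23.1 | 5.66 | 14% | 12.9 / 7.1 | 11.4 |
| B | 11.6 | 0.5 | 11.6 | 2.84 | 40% | 10.9 / 9.1 | 5.7 |
| C | 15.0 | 0.7 | 11.6 | 3.03 | 36% | 11.3 / 8.7 | 6.1 |
| D | 11.6 | 0.7 | 9.0 | 2.34 | 54% | 10.7 / 9.3 | 4.7 |

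The half-width (2.01 × SE) is also the residue still inside the 95% CI when the observed T3 difference is exactly zero. In setting A that exceeds the whole 10-point target.

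**Sequence term and either test.** These come from simulation: 40,000 trials per setting, random-intercept REML model with the period baseline as covariate, and residue of ±5 at T3 that persists, shrinks or is gone by T4.

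| Setting | Sequence term fires | Period-1 mean after it fires | Either test fires |
|---|---|---|---|
| A | 5–6% | 4.9 to 15.1 | 18–19% |
| B | 5–9% | 6.7 to 13.4 | 43–45% |
| C | 6–11% | 6.5 to 13.5 | 39–43% |
| D | 7–15% | 7.4 to 12.6 | 57–62% |

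The direction depends on which supplement leaves residue and whether it lasts to T4. The sequence term estimates the T4 residue minus the baseline slope times the T3 residue (slope 0.44 at r = 0.5, 0.65 at r = 0.7).

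**No carryover.** One of the two tests fires in 9–10% of trials. The period-1 mean stays at about 10, but its 95% CI covers the truth in 75–77% of those trials (60–64% after the sequence term alone, 85–91% after T3 alone).

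**No gate.** Always reported, the period-1 estimate averages 10.0 with 95% coverage in every setting.

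**The case against.** The case on the other side has weight.

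- *A reader might infer that most trials would show no carryover-free estimate.* The document does not support this. Section 3 puts a carryover term in the model unconditionally. By the cell algebra above, the treatment coefficient of that model is the period-1 difference; in simulated fits it averaged 9.9 to 10.2 and correlated 0.99 with the period-1 analysis. Period 1 alone is therefore not the only such estimate planned.
- *A reader might infer that the tests miss a 5-point residue in most trials.* That depends on the unstated SD and correlation and on the form of the T3 comparison. In setting D either test fires in more than half of trials. If T3 is compared with own T1 in the 25 probiotic-first participants, 5/(11.6/√25) = 2.16 standard errors gives 54% power (18% at SD 23.1). After that trigger the period-1 mean is 10.4 to 10.6 with 95% coverage at SD of difference 11.6, so the distortion is not universal. A paired comparison does, however, also pick up time trends.
- *A reader might infer that the washout evidence leaves out the probiotic.* Section 2.3 describes fructan studies and section 4 a dietary perturbation, but section 4 also cites references 57–60, which are not at hand. The point cannot be made from the documents.
- *Missed carryover does little damage to the primary estimate.* This stands. The error is half the sequence term: for a persistent 5 points, (5 − 0.44×5)/2 = 1.4 or (5 − 0.65×5)/2 = 0.9.
- *Always printing period 1 does not change its distribution given a significant test.* True, but the figure then has the stated property as a procedure, and no test decides whether it appears.
- *Unbiased here just means free of carryover.* That is a fair reading of the intent, but the sentence attaches the word to a conditional analysis, which lacks the property.

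**Conclusion.** The point holds in a limited form. The significance gate removes the property that section 3 claims for the period-1 estimate. With a 5-point residue and a true effect of 10, the gated mean is about 7 to 13 after a significant between-sequence T3 comparison. After a significant sequence term it is about 5 to 13, reaching 15 only at the larger SD. At low SD with the T3 trigger the shift is about 1 point or less. With no carryover the gated interval covers at about 75 to 80% instead of 95%.

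Power for 5 points is low at the larger SD (about 19% for either test) and may lie above or below 50% at the smaller one. The aliasing of the three model terms, and the fact that a non-significant T3 comparison cannot verify washout, need no assumed SD. The sizes rest on back-solved SDs, assumed correlations and equal variances. The primary crossover analysis is not invalidated; this is a correction to a sensitivity analysis and to the claims made for it.

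**What to change.** In section 3:
- Replace the conditional sentence with a commitment that, whatever the carryover tests show, the period-1 effect (T2 GIQLI adjusted for T1, 25 vs 25) is reported with a 95% CI as a labelled sensitivity analysis beside the crossover estimate, which remains primary.
- Report the T1-adjusted between-sequence difference at T3 with a 95% CI, and replace the verb verify with estimate.
- State that the sequence, treatment-by-period and carryover terms are one contrast, and name the one that will be reported.

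In section 4, drop the four-tier description or reduce it to the checks that are actually distinct.

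Cost: no change to visits, recruitment, samples or the primary model; two extra lines in the results table. Data collection runs to summer 2027, so the change can precede analysis. The downside is a wide period-1 interval, about ±6 to 11 points in settings A to C. At SD 23.1 it would include zero in about 60% of trials even with a true 10-point benefit, so it must not be read as a second test of superiority.

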## Abstract

Background: Gastrointestinal discomfort affects up to 70% of individuals with spinal cord injury (SCI), largely due to gut dysbiosis caused by altered transit time and reduced gastrointestinal motility from autonomic disruption. Emerging evidence links prebiotics and probiotics to improved microbiome balance and reduced inflammation, yet data in SCI remain limited. Methods: Individuals aged ≥ 18 years, with a chronic SCI (≥1 year) experiencing significant gastrointestinal symptoms, will be invited to participate in this single-center randomized controlled crossover trial. Persons currently taking antibiotics, who have relevant eating or digestive disorders, or who have undergone a recent diet change will be excluded from the study. Participants will be randomized (1:1) into two groups. The first group will take a probiotic (Biotics-G, Burgerstein AG, Rapperswil-Jona, Switzerland) supplement for eight weeks, then after a four-week washout period, they will take a prebiotic (Oat Bran, Naturaplan, manufactured by Swissmill, Zurich, Switzerland) supplement for another eight weeks. The second group will receive the supplements in reverse order. The primary outcome is the Gastrointestinal Quality of Life Index, a questionnaire to assess quality of life related to gastrointestinal disorders. Secondary outcomes consist of gastrointestinal transit time, inflammatory blood markers, and gut microbiome composition. Ethics: The study will be conducted in accordance with the Declaration of Helsinki. The study was approved by the Ethics Committee for Northwest/Central Switzerland (EKNZ, ID: 2025-00238, 24.02.2025, Version 2.0). The study is registered at ClinicalTrials.gov (ID: NCT06870331, 02.04.2025). Written informed consent will be obtained from all participants involved in the study.

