To accurately assess the potential of probiotic and prebiotic supplementation in alleviating GI discomfort, it is essential to conduct an intervention study in the broader population with SCI—particularly among those suffering from GI-related complications. The primary objective of this study is to evaluate the effect of probiotic and prebiotic supplementation in improving GI health in individuals with chronic SCI experiencing GI complaints, as measured by the Gastrointestinal Quality of Life Index (GIQLI). As secondary aims, further effects on GI health, including changes in gut microbiome composition, inflammatory serum markers, and GI transit time (GITT) will be assessed. Probiotic supplementation is hypothesized to improve GIQLI scores and decrease GITT and inflammatory serum markers, as well as increasing the relative abundance of beneficial microbial strains and decreasing inflammation-associated genera in the gut.

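### Microbiome diversity indices get paired t-tests with no period, sequence or baseline term, although the same section assigns secondary outcomes to a crossover mixed model

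*Protocol article*

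**What the plan says.** All statements are in the protocol article.

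- **Status of the outcome (Abstract).** "Secondary outcomes consist of gastrointestinal transit time, inflammatory blood markers, and gut microbiome composition".
- **General rule (section 3, Data Analyses).** "To evaluate the longitudinal variation in the primary outcome and secondary outcomes, we will use multilevel mixed-effects models". The terms are then listed: "participants are treated as random effects, while intervention and period are used as fixed effects". Each outcome's pre-period value is a covariate in every model. For carryover, "sequence (AB vs. BA) will be included as a fixed effect, and treatment-by-period interactions will be tested".
- **Diversity (same paragraph, further on).** "For the microbiome analyses, diversity indices will be compared using paired" *t*-tests, with Benjamini–Hochberg correction. The time points that form a pair are not named.
- **Proteins (same paragraph).** They are analysed by mixed models built like the primary analysis, also with false-discovery control.
- **Taxa.** The Introduction (section 1) expects the probiotic to have an effect by "increasing the relative abundance of beneficial microbial strains and decreasing inflammation-associated genera in the gut". In section 3, the only analysis that names genera is a sparse partial least-squares regression, which relates them to proteins and clinical outcomes. It is not a comparison of supplements.

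**The concern.** The article fixes two different analyses for one secondary outcome family and gives no reason for the difference. The two choices are not equivalent in a two-period crossover.

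A paired *t*-test on the T2 and T4 values removes the participant effect but not the period effect. Half the differences are shifted one way by the period effect and half the other way, and the test counts that spread as noise. If completers are unequal between sequences, part of the period effect also remains in the estimate. If the pairs are instead T1 with T2, or T3 with T4, the test measures change within a supplement. It then does not address the randomised comparison in a trial that section 2.1 calls a superiority crossover and for which section 2.3 names the prebiotic as active comparator.

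The microbiome is also where the article is most worried about such effects. Section 4 accepts that diet and lifestyle are not strictly controlled and may confound microbiome changes, and that microbial changes may persist into the second period. It relies on the statistical modelling of sequence and period as part of the answer. A paired *t*-test contains none of that modelling.

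**Working it through.** **What can be reproduced.** The article gives no power figure for diversity. Its N = 50 (25 per sequence, 85% power, 5% level, 10 points) is for the GIQLI and states no SD, so it cannot be checked. I use only N = 50, 25/25 and the 85% level, and scale everything to the SD of the within-person difference.

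**Inputs.**
- From section 2.1: N = 50, 25 per sequence, 5% level (taken as two-sided).
- Assumed: SD of the within-person difference d (probiotic minus prebiotic) = 1; period effect π (period 2 minus period 1) = 0.5 or 0.75 of that SD; a true effect of 0.432 SD, which gives 85% power at n = 50 when π = 0; completer split 24/20 for the unequal case.

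The model is d = τ − π + e in one sequence and d = τ + π + e in the other. Baseline adjustment is left out of both analyses.

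**Step 1. Balanced sequences, 25/25.** The period effect cancels from the mean of d, so there is no bias and the true variance of the mean is unchanged. The estimated variance of d, however, becomes 1 + π² × 50/49.
- π = 0.5: 1 + 0.25 × 1.0204 = 1.255, so the standard error is inflated by √1.255 = 1.120.
- π = 0.75: 1 + 0.5625 × 1.0204 = 1.574, so it is inflated by √1.574 = 1.255.

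Approximate power is Φ(0.4323 × √50 − 2.010 × inflation), where 0.4323 × √50 = 3.057 and 2.010 is the critical *t* on 49 degrees of freedom.
- π = 0: Φ(3.057 − 2.010) = Φ(1.047) = 0.85.
- π = 0.5: Φ(3.057 − 2.251) = Φ(0.806) = 0.79.
- π = 0.75: Φ(3.057 − 2.521) = Φ(0.536) = 0.70.

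Simulation agrees:

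| π (SD of d) | Paired *t*: power | Paired *t*: type I error | Period-adjusted: power | Period-adjusted: type I error |
|---|---|---|---|---|
| 0 | 85% | 5% | 85% | 5% |
| 0.5 | 79% | about 2.9% | 85% | 5% |
| 0.75 | 70% | about 1.4% | 85% | 5% |

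**Step 2. Unequal completers.** In absolute size, the bias of the mean of d is π × (difference in completers) / (total completers). At 24/20 this is π × 4/44 = 0.09π, which is 0.045 SD at π = 0.5 and 0.068 SD at π = 0.75. If the bias opposes the treatment effect, simulated power of the paired test is 62% or 46%, against 80% for the adjusted analysis. If it runs the same way as the effect, paired power is about 81% or 78%. Type I error of the paired test is about 3.5% at π = 0.5. At a more extreme 24/16 split with π = 0.5, the bias is 0.10 SD and type I error is 6.0%.

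**Step 3. The pre-post reading.** No arithmetic applies. A test of T1 against T2, or T3 against T4, within one supplement estimates change from baseline under that supplement and contains no contrast between supplements.

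**The case against.** **A specific rule may override a general one.** The diversity sentence can be read as a deliberate exception, or as a supplement to the mixed models, since nothing says that diversity is excluded from them. That is possible. But no reason is given, and the proteins, in the same paragraph, are explicitly kept on the model. On either reading the two sentences need to be reconciled.

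**The taxon hypothesis.** A reader might infer that the directional hypothesis about strains and genera goes untested. The documents do not support that. The general sentence on secondary outcomes nominally covers gut microbiome composition, and the paired-test sentence names only diversity indices. A condensed article may leave the differential-abundance method to the analysis plan. What remains is that no taxon-level comparison between supplements is spelled out.

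**Drift credited to the supplement.** A reader might also infer that the paired test would produce false positives. At 25/25 there is no bias and the test is conservative. It stays below 5% at 24/20, and mild inflation appears only at a split such as 24/16. Blocks of four keep enrolment close to balance. The main cost is power.

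**Size of the power loss.** Putting the inflated variance into a standard power formula gives 76% and 67%. That overstates the loss, because with fixed balanced sequences only the estimated variance grows, not the true variance of the mean.

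**Incomplete pairs.** Dropping them is consistent with the article's available-data rule. A mixed model would keep a one-period participant only if that period's baseline is also present, so the gain is modest and I do not rest the point on it.

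**Conclusion.** The inconsistency stands. Section 3 states a crossover mixed model for secondary outcomes, then gives diversity indices a test without period, sequence or baseline and without naming the pairs. If T2 and T4 are paired by supplement, the expected harm is loss of power and a conservative test: from 85% to about 79% or 70% at period effects of 0.5 or 0.75 SD with 25/25. Bias is a secondary risk that depends on unequal completers. If the pairing is pre-post within a supplement, the test does not answer the trial's question.

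The period effects and completer splits are assumptions; the article documents neither. With no period effect and balanced completers, the two analyses perform alike apart from the baseline adjustment. The point concerns one secondary outcome family. The GIQLI analysis is not affected.

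**What to change.** - Replace the paired *t*-tests for diversity indices with the model already planned for the other secondary outcomes: participant random; intervention, period and sequence fixed; pre-period baseline as covariate. Keep Benjamini–Hochberg correction across the diversity indices.
- State that the taxa named in the Introduction's hypothesis get the same between-supplement comparison. The differential-abundance method can be left to the analysis plan.

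The cost is a change of wording and a little modelling work, since the same model is to be fitted for the other outcomes. Section 2.1 expects data collection to run to summer 2027, and the change needs no new data.
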